## Background

Prostate Cancer (PC) is the most frequent diagnosed malignancy in men in Europe and North America. The risk of PC increases with age, and the median age of onset is approximately 70 years. Treatment depends on stage, histology and the serum PSA level, beside the patients' general health and age. Radiotherapy combined with androgen deprivation therapy (ADT) is used in patients with locally advanced tumors and/or those with high Gleason scores, characterized as intermediate or high-risk profiles [1]. ADT has potentially negative effects on several clinical outcomes, such as muscle atrophy [2].

Physical exercise during and after cancer treatment has been shown to be effective to reduce several negative clinical consequences followed by cancer and cancer treatment [3,4]. Compared to breast cancer patients relatively few studies in PC patients have been published [4,5]. More evidence on the efficacy of strength training on clinical outcomes in PC patients is therefore desirable. At the same time more attention should be paid to the effect of ADT on the muscle cell level because the reduced testosterone levels influence the underlying regulators of muscle mass and muscle function. Furthermore, the effects of strength training on the same regulators are of particular interest during ADT, and as far as we know they have not previously been explored in PC patients.

Ageing is associated with a reduction in muscle mass, typically by 1-2% per decade from the age of 30 to the age of 50. Thereafter the rate of muscle loss increases progressively to 10% per decade [6]. It is well known that decreased levels of serum testosterone are followed by reduced muscle mass [7,8]. In PC patients treated with ADT for 6-12 months, lean body mass (LBM) has been reported to decrease by 3% [9]. This reduction may affect muscle strength markedly because muscle mass is the dominant tissue in LBM.

Loss of bone mineral density (BMD) has been observed in PC patients on ADT [10,11]. It has also been shown that ADT increases body weight and fat mass in these patients [9]. Decreased levels of testosterone and body changes during ADT, may also influence mental health, fatigue and health-related quality of life (HRQOL) in PC patients [12,13].

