### Outcomes and assessments

Both clinical and muscle cellular outcomes are collected before the intervention (pre-intervention assessments) and after the intervention (post-intervention assessments) (Figure 3). All outcomes, specific variables and assessments in the PEPC trial are listed in Additional file 3.

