### Sample size and statistical considerations

LBM is the primary endpoint of the study. Sample size calculation is based on comparing the clinically relevant difference in change before and after the 16 weeks period in LBM between the EG and CG. To detect a 3 kilograms difference in change between the groups, and assuming a standard deviation (SD) of 3 kilograms, 22 patients are needed in each group with a significance level (two sided) of 5% and a power of 90%. Due to dropouts we plan to include 30 patients in each group. According to previous studies, this number should also be sufficient to detect differences in the cellular muscle outcomes (Sinha-Hikim et al., 2006).

Changes in outcome variables from start of intervention will be compared between the EG and CG groups by analysis of covariance using the baseline measurement as a covariate. P-values below 5% will be regarded as statistically significant. If obvious deviations from normal distributions are detected, changes in outcome will be compared between groups by Wilcoxon-Mann-Whitney test. The primary analysis population will be the intention to treat population using last observation carried forward to impute any missing values. In addition a per-protocol analysis including only patients with no missing observations of the variable of interest will be performed. Should imbalances in important variables be detected sensitivity analyses will also be added including these as covariates in the model.

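### With one assessment before and one after training, the primary last-observation-carried-forward rule sets every dropout's lean body mass change to 0 kg and, at the implied dropout allowance, biases the primary estimate

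*Protocol article*

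**What the plan says.** All references are to the protocol article. Under *Sample size and statistical considerations*, "LBM is the primary endpoint of the study". Change is compared between arms by analysis of covariance with the baseline value as covariate, and the rule for missing data is: "The primary analysis population will be the intention to treat population using last observation carried forward to impute any missing values". A supplementary analysis, labelled per-protocol, keeps only patients with no missing value of the variable concerned.

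Under *Outcomes and assessments*: "Both clinical and muscle cellular outcomes are collected before the intervention (pre-intervention assessments) and after the intervention (post-intervention assessments"). *Participants* places the repeat assessment one week after the intervention period. *Randomization* places allocation after the pre-intervention assessments, so every randomised patient should have a baseline value. No intermediate body composition scan is described.

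On dropout, the sample size section says only: "Due to dropouts we plan to include 30 patients in each group". The *Background* notes that, in patients on androgen deprivation for 6-12 months, "lean body mass (LBM) has been reported to decrease by 3" per cent.

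**The concern.** Carrying the last observation forward presupposes an intermediate visit. Here there is none, so the rule amounts to baseline carried forward, and each missing change is replaced by exactly 0 kg and analysed as if measured. Zero is not what the protocol expects in either arm: it cites LBM loss on androgen deprivation, which continues throughout, and it is designed to show a gain with training.

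The rule governs the primary analysis of the primary endpoint, so it determines the headline estimate and its interval. Attenuation matters more than usual here, because the *Discussion* asks whether the muscle-building response is blunted at castrate testosterone levels. A diluted estimate could be mistaken for such blunting.

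**Working it through.** **Inputs from the protocol.** Difference in change: "To detect a 3 kilograms difference in change between the groups". SD of change: "assuming a standard deviation (SD) of 3 kilograms". Sample size: "22 patients are needed in each group with a significance level (two sided) of 5% and a power of 90" per cent. Planned: 30 per arm.

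**Assumptions.** The dropout rate is inferred: (30 − 22)/30 = 8/30 = 26.7%. Unless noted, dropout is unrelated to outcome. The simulations (8,000 trials per scenario) assume a baseline SD of 7 kg.

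**1. The plan's own figure.** n = 2 × (1.960 + 1.282)² × 3²/3² = 21.01, rounded up to 22 per arm. The two-sample t-test has 89.97% power at 22. Also 22/(1 − 8/30) = 30. Both figures reproduce.

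**2. Expected estimate, equal dropout.** With a fraction d set to zero in each arm, the expected difference is (1 − d) × true difference. At d = 8/30: 22/30 × 3 = 2.2 kg, a bias of −0.8 kg (−27%). At d = 0.10: 2.7 kg. At d = 0.20: 2.4 kg.

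**3. Standard error (exercise mean change 3 kg, control 0).** Variance of the part-imputed changes:
- Exercise: 22/30 × (9 + 9) − 2.2² = 8.36
- Control: 22/30 × 9 = 6.60
- SE = √(8.36/30 + 6.60/30) = 0.71
- Observed values only: SE = √(9/22 + 9/22) = 0.905

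**4. Simulated analysis of covariance, true difference 3 kg, equal dropout.**

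| Missing per arm | Analysis | Mean estimate | Mean SE | Coverage of 3 kg | Power |
|---|---|---|---|---|---|
| 8/30 | carried forward | 2.20 kg | 0.71 | 81% | 0.88 |
| 8/30 | observed values | 3.00 kg | 0.91 | 95% | 0.89 |
| 6/30 | carried forward | 2.40 kg | 0.73 | 88% | 0.91 |
| 3/30 | carried forward | 2.71 kg | 0.76 | 94% | 0.95 |

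With mean changes of +1.5 and −1.5 kg and 8/30 missing, carrying forward gives 2.21 kg, 80% coverage and power 0.90; observed values also give power 0.90.

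**5. Source of the undercoverage.** In the first row of the table, the empirical SD of the carried-forward estimate is 0.67 against a mean model SE of 0.71, so the SE is not too small for that estimator. Its interval covers 2.2 kg 96% of the time. The shortfall for 3 kg comes from the shifted centre.

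**6. Type I error.** With equal dropout of 8/30 and no effect it is 5.1% (no change in either arm) or 3.9% (1.5 kg loss in both), so it is not inflated.

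With unequal dropout and a common loss L in both arms, the spurious effect is L × (exercise dropout − control dropout). Take an assumed split of 12/30 v 4/30, a gap of 8/30, and an assumed 57 kg of LBM:
- The cited 3% loss refers to 6-12 months, and 16 weeks is about 3.7 months. Pro rata: 3% × 3.7/12 = 0.92%, or 0.53 kg; 3% × 3.7/6 = 1.85%, or 1.05 kg.
- Spurious effect in favour of exercise: 0.53 × 8/30 = 0.14 kg to 1.05 × 8/30 = 0.28 kg. Simulated type I error: 5.2-6.6%.
- If the full 3% (1.7 kg) occurred within 16 weeks: 1.7 × 8/30 = 0.45 kg, type I error about 9%.

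If the dropout split is reversed, the sign reverses.

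**The case against.** **The standard error and interval.** A reader might infer that imputed zeros always make the standard error too small. Step 5 does not support that. The interval is narrower than that of the observed-data analysis (2.84 v 3.67 kg), but it is adequate for the quantity this estimator targets. The fault is bias.

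**False positives.** A reader might also infer that the rule inflates the type I error to about 9%. That needs a 6-12 month loss compressed into 16 weeks together with a threefold dropout imbalance, and the protocol supports neither. It even offers controls the programme afterwards to limit dropout. At a 10 v 6 split, type I error stayed between 4.3% and 5.3%, even with a 1.7 kg loss.

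**What is being estimated.** The 27% figure assumes that men who drop out would have had the same mean change as those observed in their arm. If exercise dropouts gained nothing from training and dropout were equal, the effect among all randomised men would itself be 22/30 × 3 = 2.2 kg. This objection stands as a condition on the figure. It does not rescue the rule: agreement would rest on dropouts gaining nothing at all from completed sessions, and on balanced dropout if LBM is falling.

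**Existing safeguards.** The supplementary analysis is in effect the observed-data analysis, so a discrepancy would be visible, and power hardly differs. Both points are fair. But that analysis is secondary and labelled per-protocol, and the article does not say how a disagreement would be resolved.

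**Cellular outcomes.** A reader might think the rule would impute patients who were never biopsied. They have no value to carry forward, so it would not.

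**Conclusion.** The concern holds as a bias in the primary estimate. That each missing change becomes exactly 0 kg follows from the two-visit design and needs no outside assumption. With 8/30 missing per arm, unrelated to outcome, a true 3 kg is reported as 2.2 kg on average, with about 80% coverage, and the imputed values buy no power. The 8/30 is inferred from the inflation of 22 to 30 and is not a stated forecast; at 10% dropout the effect is minor.

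The direction is not fixed. Equal dropout dilutes the effect without inflating type I error. Unequal dropout with LBM loss in both arms can create a modest spurious effect favouring the arm with more dropouts: 0.14-0.28 kg with type I error 5.2-6.6% under pro rata losses and the assumed 12 v 4 split.

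**What to change.** Replace the missing-data sentence. Make the primary analysis an analysis of covariance by assigned arm, regardless of training adherence, that is valid under missing at random. It can use all observed post-intervention values, a likelihood-based model of baseline and post values, or multiple imputation by arm.

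State that the already planned post-intervention scan is sought from every randomised patient, including those who stop training. This also reduces dependence on the missing-at-random assumption. Keep baseline carried forward only as a sensitivity analysis.

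The cost is revised wording, a little programming and a wider interval (about 3.67 kg instead of 2.84 kg at 8/30 missing when observed values are used). No new visit and no change in sample size are needed: 22 observed per arm still gives about 0.89-0.90 power.

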## Discussion

Previous research has examined the effect of physical exercise on clinical outcomes such as body composition, physical function, mental health, fatigue and quality of life in PC patients [3-5]. Still research on the effect of physical exercise in this patients group is less extensive than in other cancer groups, such as for example patients with breast cancer. Two of the most pronounced clinical side effects of ADT are the negative effect on muscle mass and muscle strength. However, studies investigating the effects of ADT and exercise at the muscle cell level are still lacking. Expanded knowledge in this field among PC patients is therefore required.

The clinically indicated ADT in PC patients enables the study of testosterone's role in regulation of muscle mass during strength training. The main question is whether normal adaptations to strength training are disturbed when the level of testosterone is below 1 nmol/L (castration level); e.g. is the activation of satellite cells and hypertrophic effect of strength training blunted in these patients? Furthermore, by investigating important factors for the regulation of muscle mass and muscle function, the cellular effects of ADT on muscle tissue will be elucidated. Currently, three other ongoing trials are investigating the effect of exercise on muscular outcomes assessed by muscle biopsies in patients with breast, lung and testicular cancer receiving chemotherapy [52-54]. However, the effects of high-load strength training on muscular adaptations in PC patients during ADT have not previously been investigated.

Compared to previous studies in PC patients the intensity and/or duration in our strength training protocol is somewhat increased [44,55,56]. The rationale for choosing a strenuous strength training protocol is the fact that the effect on total muscle mass has been moderate or absent in previous studies on PC patients. One possible explanation for negligible effects on muscle mass in previous studies may be that the stimuli for muscle hypertrophy have been too low. In healthy men, it is suggested that a training intensity of 75-80% of 1 RM (6-12 RM sets) combined with multiple sets in each exercise (starting from 1-2 and progressing to 3-6 sets per exercise), give optimal stimuli for muscle hypertrophy when performed 2-3 times per week [57]. Consequently, in order to maximize the stimuli for muscle hypertrophy we chose to implement this strength training protocol in our patients. Importantly the training protocol should still be tolerable and safe.

Positive findings from the PEPC trial will help in the construction of more effective training protocols to counteract the negative effects of ADT on muscle tissue, BMD and physical function. More importantly, the results on the cellular effects of ADT in muscle tissue will provide novel understandings of muscle mass regulation by testosterone. Such knowledge will improve our understanding on how aging in general and reduced testosterone production during ADT specifically, induces loss of muscle mass (sarcopenia). In turn this knowledge can be used to establish more effective strategies against sarcopenia in both healthy elderly and in patient populations at risk. New strategies could include both new medical treatments and training strategies focused to overcome the cellular changes inducing sarcopenia.

### Summary

Knowledge of the effect of exercise on clinical outcomes such as physical functioning and quality of life outcomes has increased over the last decades. Studies testing aerobic exercise in breast cancer patients are most frequent. Studies in other cancer groups testing the effects of strength training program are still lacking. The PEPC trial focuses on the effect on a high-load strength training program on both clinical and muscle cellular outcomes in PC patients during ADT. As far as we know this is the first study having a muscular cellular outcome in these patients. By testing a high-load strength training program the study will provide new knowledge on optimal training programs in PC patients.

## Endnote

^1^The term muscle fiber (muscle cell) originates from the embryonic formation of mature muscle cells where mononuclear myoblasts fuse to the giant multinuclear muscle cells.
